## Abstract

**Background:**

Despite successes in preventing and treating HIV, Indigenous people in Canada continue to face disproportionately high rates of HIV infection. Programs that support healing from lifetime trauma, support connection to culture, and reduce drug-related harms are critical to preventing HIV among young Indigenous people who use drugs. The Cedar Project WelTel mHealth intervention proposed here is a structured mobile-phone initiative to connect young Indigenous people who use drugs with Cedar Case Managers in a community-based setting. The intervention consists of a package of supports, including a mobile phone and cellular plan, weekly two-way text messaging, and support from Cedar Case Managers.

**Methods:**

The Cedar Project WelTel mHealth study is a multi-site Zelen pre-randomized trial to measure the effect of a two-way supportive text-message intervention to reduce HIV vulnerability among young Indigenous people who use illicit drugs in two Canadian cities. The trial is nested within the Cedar Project, an ongoing cohort study addressing HIV and hepatitis C vulnerability among young Indigenous people who use drugs in Vancouver and Prince George, British Columbia. The Cedar Project Partnership, an independent body of Indigenous Elders, leaders, and health/social service experts, governs all aspects of the study. Two hundred participants will be followed over a 16-month period, with HIV propensity score at 6 months as the primary outcome. Secondary outcomes include HIV propensity at 1 year, HIV risk, resilience, psychological distress, access to drug-related services, and connection to culture measured at 6 months and 1 year. Primary analysis is by intention to treat.

**Discussion:**

Culturally safe interventions that address barriers to HIV prevention while supporting the strength of young Indigenous people who use drugs are urgently needed. Despite presenting a tremendous opportunity to connect young, highly transient Indigenous people who use drugs to prevention services, supportive two-way mHealth programs have yet to be tested for HIV prevention in a community-based setting with this population.

**Trial registration:**

ClinicalTrials.gov NCT02437123 https://clinicaltrials.gov/show/NCT02437123 (registered 4 May 2015). Protocol version: 24 July 2015.

## Background

Indigenous scholars suggest that understanding substance use and HIV vulnerability among young Indigenous people must begin with consideration of the ongoing impact of colonization and intergenerational trauma while also acknowledging strength and survival in the face of incredible hardships [1–5]. Indigenous scholars have described intergenerational trauma as a collective emotional and psychological “soul wound” that continues to affect the youngest generations of Indigenous people [6, 7]. In Canada, well over 150,000 Indigenous children were forcibly removed from their homes and placed in residential schools between 1883 and 1996 [8]. The persistent devaluation of Indigenous cultural identity and widespread physical, sexual, and emotional abuse that occurred at residential schools has had far-reaching consequences for the health of Indigenous people [9]. Many Indigenous scholars and advocates argue that cultural oppression through the removal of children from their families and communities has continued through the child welfare system [10]. In fact, estimates indicate that three times as many Indigenous children are currently in care of the state compared with during the peak of the residential school system in the 1940s [10]. In a study of young Indigenous people who use drugs in British Columbia (BC), 65 % had been removed from their biological parents and placed into care [11]. Those who had been in care were 2.1 times more likely to have a parent who attended residential school and 2.6 times more likely to have been sexually abused. The residential school and child welfare systems in Canada disrupted ways of life that had sustained Indigenous families and communities over generations, and introduced cycles of multi-generational grief, trauma, and displacement [10]. Acknowledging the profound effect of intergenerational and lifetime trauma, and subsequent reliance on the powerful numbing effect of drugs, is critical to understanding HIV vulnerability among young Indigenous people who use drugs [4, 7, 12–15].

Indigenous leaders in Canada are justifiably concerned about alarming rates of HIV infection among their young people who continue to be vastly over-represented in the HIV epidemic [16]. Although Indigenous people comprise just 3.8 % of Canada’s total population, Indigenous people in 2013 represented 16 % of positive HIV tests in the country [17]. Injection drug use remains the primary exposure among Indigenous people, accounting for 64 % of HIV infections, compared with 11 % among non-Indigenous people [16]. In addition, one third of new infections were among young Indigenous people under 30 years of age, compared with only 20 % among young non-Indigenous people [16]. There is a continuing crisis of HIV infection among young Indigenous people who use injection and non-injection drugs in BC; HIV prevalence reached 9 % overall and 17 % among those who inject drugs [12]. In addition, HIV incidence among young Indigenous people who use injection drugs in BC is estimated to be three times higher than among non-indigenous young people [18].

Significant and multi-layered barriers to HIV prevention services, including health care, harm reduction, addiction treatment, and safer sex work environments, have been identified among young Indigenous people who use drugs [2, 3, 12, 13]. Young Indigenous people who use drugs have described frequent encounters with systemic and interpersonal racism, stigma and judgement within harm reduction and health services [1, 19–23]. Furthermore, despite compelling evidence that harm reduction programs, including supervised drug consumption facilities [24] and opioid substitution therapy [25], are effective at preventing HIV infection, studies indicate that young Indigenous people are failing to engage with these services [12, 18, 26, 27]. Finally, safety in sex work, as well as supports to leave sex work if desired, remains elusive in a country where young Indigenous women in sex work routinely face extreme violence and death in the course of their work [28, 29].

Addressing barriers to HIV prevention among young Indigenous people who use drugs—while also acknowledging resilience despite adversity—is urgently required. In New Zealand, Maori nurses have emphasized the need for health care that is “culturally safe” in order to overcome power imbalances that shape interactions between health-care providers and Indigenous clients [30]. Culturally safe care simultaneously privileges Indigenous worldviews and acknowledges the impact of structural violence experienced by colonized peoples in health-care settings [31]. Indigenous experts also recognize the importance of “culture as intervention” to support resilience and resistance to HIV infection as well as trauma-informed counseling as a response to the harmful effects of historical and lifetime trauma [1]. Others have noted the critical role of interconnectedness with family and community to support health and healing among Indigenous individuals [32]. Further research has highlighted the importance of non-medical, supplementary support for young Indigenous people in order to break through layers of marginalization experienced in their everyday lives [33].

Mobile health (mHealth), the provision of health care via mobile phones, has been identified as potential tool to support young drug-using Indigenous people to overcome barriers to HIV prevention. Recent trials in sub-Saharan Africa have provided evidence that supportive text-message interventions can improve HIV treatment adherence and viral suppression among people living with HIV [34, 35]. Others have begun to investigate the impact of mHealth for HIV care and treatment among people living with HIV who use drugs [36–38]. However, much of the existing evidence on mHealth interventions for HIV prevention has focused on improving HIV knowledge by delivering HIV prevention messages to diverse at-risk groups [39]. To our knowledge, no studies have investigated the potential for a two-way supportive text-message program to reach out to young drug-using Indigenous people to reduce vulnerability to HIV infection.

This protocol outlines a multi-site Zelen pre-randomized trial to measure the effect of a culturally safe, two-way supportive text-message intervention to reduce HIV vulnerability among young Indigenous people who use illicit drugs. This work will build on findings from recent studies implementing mHealth interventions in HIV clinics in Nairobi, Kenya and Vancouver, Canada [34, 40]. Outcomes include HIV propensity score, HIV risk, resilience, psychological distress, access to drug-related services, and connection to culture. We hypothesize that the Cedar Project WelTel mHealth intervention will result in improved uptake and access to HIV prevention services, including health-care, harm reduction and addictions services, cultural supports, housing, and counseling. We believe that, together with the supportive element that “someone cares” enough to check in each week, improved access to services will help strengthen participants’ resilience and reduce vulnerability to HIV infection.

## Methods and design

### Study design

The Cedar Project WelTel mHealth study is a two-site, two-arm, parallel group, open, stratified Zelen pre-randomized controlled trial to measure the effect of a culturally safe, two-way supportive text-message intervention to reduce HIV vulnerability among young Indigenous people who use illicit drugs in a community-based setting (ClinicalTrials.gov identifier NCT02437123). Participants will be pre-randomized to two groups—either the mHealth intervention or standard care—at a 1:1 allocation ratio.

### Study setting

This trial is a sub-study nested within the Cedar Project, a cohort study of young Indigenous people who use injection and non-injection drugs and reside in Vancouver and Prince George, BC, Canada. Initial recruitment into the Cedar Project occurred between 2003 and 2007 and was re-opened in 2011. To date, 738 participants have enrolled in the main Cedar Project cohort in Vancouver and Prince George. Eligibility criteria included being between the ages of 14 to 30 at enrollment, provision of informed consent, self identification as having Indigenous ancestry, and smoking or injecting drugs—including crystal methamphetamine, opiates, crack or cocaine—at enrollment. Cedar Project participants complete an enrollment visit as well as follow-up visits every 6 months. At each study visit, participants complete detailed questionnaires eliciting demographic, behavioural and health information, administered by trained Indigenous interviewers. Participants also provide a venous blood sample for HIV and hepatitis C virus antibody testing. In gratitude for participants’ time, honoraria are provided at each follow-up visit. The Cedar Project has been approved by the University of British Columbia Providence Health Care Research Ethics Board (H02-50304).

The Cedar Project study storefront research offices are located in Vancouver’s downtown eastside and in the downtown core of Prince George. Vancouver is a large city in southern BC and is located on the traditional territory of the Coast Salish peoples. Prince George is a forestry and mining town in the province’s northern interior, located on the traditional territory of the Lheidli T’enneh people. Cedar Project participants represent many of the diverse First Nations, Inuit and Métis communities across Canada and are often living far away from their home communities. Participants are highly transient, moving frequently between cities and reserves, making continuity of care a tremendous challenge [41]. Indigenous interviewers and nurses support both sites and are encouraged to provide referrals to cultural supports, health care, substance use services, food programs, housing, and counseling for participants who seek them.

### The Cedar Project Partnership model

Since its inception, the Cedar Project has been community-driven, interdisciplinary research that responds to the continuing crisis of HIV infection and contributes to the health and healing of young Indigenous people who use drugs. The Cedar Project Partnership, an independent body of Indigenous Elders, health and social service experts, researchers, and elected leaders, governs the entire research process. The Cedar Project Partnership recognizes that conducting culturally safe research with young, vulnerable Indigenous people requires creating safe spaces where their identities, voices and stories are heard and respected [30]. A critical component of the Cedar Project is to ensure that our site offices are safe, welcoming settings without judgement of drug use, where police are not allowed, and cultural identity is honoured. Part of building cultural safety into the Cedar Project includes supporting access to traditional foods and ceremonies, such as through annual feasts, memorials, and a recent Learning Potlatch to honour our partners and participants held in Prince George. Overall, our paradigm is to acknowledge grief and historical trauma while building on young Indigenous peoples’ strengths.

### Participants

A stratified random sample of participants in the Cedar Project cohort will be selected for participation in the Cedar Project WelTel mHealth study (Fig. 1). A sampling frame of eligible Cedar Project participants will be created on the basis of the following eligibility criteria:

**Fig. 1 Fig1:**
[figure not shown]
Cedar Project mHealth Study for HIV prevention CONSORT diagram of study design

 Currently enrolled in the Cedar Project Completed main Cedar Project baseline questionnaire and attended at least one follow-up visit since 2009 Had not tested positive for HIV Joined study in Vancouver or Prince George Alive at initiation of the Cedar Project WelTel mHealth study.

Participants who do not meet the eligibility criteria or who decline to participate will be excluded. Stratified randomization in a 1:1 ratio will be used to ensure a balance of key factors, including study site (Prince George and Vancouver) and reporting injection drug use at the last visit (yes versus no). Sampled participants will be randomly assigned to receive the intervention or be included in the comparison group through computer-generated codes developed by a statistician at the Centre for Evaluation and Outcome Sciences at St. Paul’s Hospital. A list of participants to be invited into the intervention arm will be distributed to each study site. Informed consent will be sought from each participant invited to receive the intervention who agreed to participate. Those assigned to the comparison group will continue in the usual Cedar Project cohort study under its existing informed consent with no change whatsoever to their participation in the overall study. Target enrollment is set at 200 participants.

#### Intervention group

To ensure that we reach our target sample, initial randomization will be slightly unbalanced to accommodate refusals to participate or difficulty locating participants. A total of 140 participants (70 from each site) will be randomly allocated to receive the invitation to participate in the intervention arm of the mHealth study. This will allow for an estimated 20 participants per site who cannot be reached or who decline to participate. Cedar staff will invite and enroll participants from this list to join the study until enrollment reaches 50 at each study site. Three attempts will be made to invite participants in the intervention arm into the study, including during regular visits to the research offices, phone, email, word of mouth, and street outreach.

#### Comparison group

One hundred Cedar Project participants who meet the eligibility criteria will be allocated to serve as the cohort comparison group, stratified on the same variables used to select the intervention group. Participants randomly assigned to the control group will continue as Cedar Project participants under usual circumstances. This group of cohort controls will not be required to provide any additional data to the study beyond that which they provide in semi-annual follow-up interviews as participants in the main Cedar Project study.

### The intervention

The Cedar Project WelTel mHealth intervention being evaluated is a structured mobile-phone initiative to connect young Indigenous people who use drugs with Cedar Case Managers in a community-based setting. The intervention consists of a package of supports, including a mobile phone and cellular plan, weekly two-way text messaging, and support from Cedar Case Managers. The intervention will be implemented over a 16-month period, and all participants will receive the intervention for a minimum of 6 months.

Cedar Case Managers include Indigenous and non-Indigenous nurses and Cedar Project staff members who have extensive frontline outreach experience with young Indigenous people who use drugs in Prince George and Vancouver. Cedar Case Managers follow a “culturally safe” approach that acknowledges both trauma and strengths and includes an explicit focus on the critical roles of cultural assets and safe relationships with care providers in HIV risk reduction [31].

Participants allocated to receive the intervention will be provided with a cellular phone at the start of the study. Each phone is pre-programmed with several phone numbers for emergency and health-related services relevant to the study site. During the study period, participants will receive a monthly cellular plan that includes unlimited calling and texting within Canada, but no data. We made an explicit decision to include long-distance calling and texting to provide the opportunity for participants to connect with family and loved ones living in home communities and elsewhere in Canada. If phones are lost or stolen, participants will be eligible to receive one replacement. If two phones are lost, the participant may bring their own sim card-enabled cellular handset to use with the study monthly cellular plan.

The supportive text-message component of the study is based on the intervention tested in the WelTel Kenya1 trial (Fig. 2) [34]. Each Monday at noon, a text message saying, “How’s it going?” is automatically sent to intervention arm participants through the WelTel mHealth software platform. Cedar Case Managers will login within 24 to 48 hours to triage the incoming text messages. They will respond to all participants and follow up with participants who replied with a specific problem or need. On Wednesday, participants who have not replied will receive an additional text saying, “Haven’t heard from you, are you OK?” On Thursday or Friday, staff will attempt to call all remaining participants who have not responded by text message. Throughout, study staff will keep a log of all responses and actions taken through the WelTel platform.

**Fig. 2 Fig2:**
[figure not shown]
The Cedar Project WelTel mHealth intervention

### Blinding

We recognize that blinding in a trial such as ours is challenging. Care providers (Cedar Case Managers) and intervention arm participants cannot be blinded, as the mHealth intervention requires overt participation and an “invite list” is provided upfront. However, participants in both the intervention and control groups will be blinded to specific study hypotheses. Primary and secondary outcomes will be drawn from routine data collection that occurs as part of participation in the overall cohort; it is unlikely that participants will identify the specific questions used to generate outcomes from our extensive questionnaires. The data analyst will also be blinded to group allocation.

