### Statistical analysis

The analysis and reporting of the results will follow the CONSORT (Consolidated Standards of Reporting Trials) guidelines [44]. Descriptive statistics of socio-demographic, historical/lifetime trauma, sex- and drug-related HIV vulnerabilities, and health-related variables will be presented to assess comparability of the intervention and control groups. Mean (standard deviation) or median (quartiles) will be used for continuous variables and count (percentage) for categorical variables. Our primary analysis to evaluate the effect of the mHealth intervention on HIV prevention will be by intention to treat (ITT) for primary and secondary outcomes among all randomly assigned participants according to the study group to which they were originally allocated. Student’s *t* tests and chi-squared tests will be used to determine differences in the mean change in proportions or scores from baseline at 6 months or 1 year between the two study arms. If baseline characteristics are found to be substantially different between the two study arms, we will adjust for these factors by using regression models. In addition, we will conduct a secondary analysis by using a modified ITT approach including only participants who agreed to participate in the intervention making up the intervention group (excluding over-sampled participants who did not receive the intervention). To minimize the risk of bias introduced in our modified ITT analysis, we propose to use complier average causal effect (CACE) analysis [45]. This approach will allow us to retain the initial random assignment by taking into account two subgroups within the group pre-randomized to receive the intervention (those who did and did not actually receive the intervention) and then helping us to identify a similar subgroup of control participants who could have been expected to receive the intervention had it been offered [45]. By comparing expected and observed outcomes in these subgroups, we will obtain a less biased estimate of effect of the intervention [45]. Missing data will be approached by using multiple imputation. An up-to-date version of R statistical software will be used to conduct all analyses [46]. All tests will be two-sided; *P* values of less than 0.10 will be considered significant. We plan to conduct four predetermined exploratory subgroup analyses that may help to tailor the intervention for specific high-need populations, including comparisons by gender, city, injection drug use, and urban versus rural. Statistical methods similar to those described above for whole-group analyses will be conducted for primary and secondary outcomes. All subgroup results will be reported, regardless of significance. Inferences will be hypothesis-generating, given concerns related to multiple comparisons and lower power to detect an effect in subgroups.

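### The protocol claims a blinded data analyst, but arms of 140 and 100 can be told apart by a count and the CACE analysis needs data that only the invited arm has; the baseline-adjustment rule is the stated choice exposed to this.

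*Protocol article*

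**What the plan says.** The Blinding section accepts that case managers and intervention participants cannot be blinded, says that both groups will be blinded to the specific hypotheses, and adds: "The data analyst will also be blinded to group allocation". It describes no stage, procedure or division of work.

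The arm sizes are given under Intervention group ("A total of 140 participants (70 from each site) will be randomly allocated to receive the invitation") and Comparison group ("One hundred Cedar Project participants who meet the eligibility criteria will be allocated to serve as the cohort comparison group"). The inequality is intended: "initial randomization will be slightly unbalanced to accommodate refusals to participate or difficulty locating participants". The Participants section nevertheless says "Stratified randomization in a 1:1 ratio will be used to ensure a balance of key factors".

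Under Statistical analysis, the primary analysis is by intention to treat "among all randomly assigned participants according to the study group to which they were originally allocated", with multiple imputation for missing data. A secondary modified analysis and a CACE analysis follow. The latter works with "two subgroups within the group pre-randomized to receive the intervention (those who did and did not actually receive the intervention"). The rule for adjustment reads: "If baseline characteristics are found to be substantially different between the two study arms, we will adjust for these factors by using regression models".

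**The concern.** The blinding sentence states a property of the trial, and the rest of the design appears to remove it. An analyst given arms coded A and B need only tabulate them to see which is the invited arm. An analyst who runs the CACE model must know it.

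What is at stake is the decision on adjustment. With neither a threshold nor a list of candidate factors, someone has to judge which baseline differences are large enough to enter the model. Where a factor's relation to the score is already known from the cohort, a person who knows the arms can often guess which way adjustment will move the estimate, even before seeing outcomes. The trial is open and most of its outcomes are self-reported. Analyst blinding is the only blinding to allocation that the protocol affirmatively claims for the study team, and readers of the trial report would give it credit.

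**Working it through.** **The plan's own sample size.** Inputs from the Sample size section: d = 0.40, one-sided alpha 0.05, power 80 %, equal arms.

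- Normal approximation: n = 2(1.645 + 0.842)² / 0.40² ≈ 77.3 per arm. The t-test solution is 77.97, so 78, as stated.
- With 20 % attrition: 78 / 0.80 = 97.5, so 98, rounded up in the plan to 100 per arm.

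The 100 per arm is therefore an enrolment target. It is not the size of the randomised arms.

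**Randomised arms.** Invited: 70 × 2 = 140. Comparison: 100. The ratio is 140 / 100 = 1.4 and the difference is 40 people. The primary set is all randomised as allocated, and imputation keeps those denominators. A baseline table by arm, which the adjustment rule needs, shows them too.

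The number of controls per site is not stated. If the 100 are split equally, the count is 70 v 50 at each site; that split is an assumption and nothing below needs it.

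**Would attrition hide the difference?** At the plan's 20 % in both arms, expected completers are 140 × 0.80 = 112 and 100 × 0.80 = 80. Completer counts were simulated as binomial, 400,000 trials per row. Only the first row uses the plan's attrition figure for both arms; the other rows are assumptions.

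| Attrition, invited v control | Trials in which the invited arm is not the larger |
|---|---|
| 20 % v 20 % | none |
| 30 % v 20 % | about 0.5 % |
| 30 % v 10 % | about 11 % |
| 40 % v 10 % | about 84 % |

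With 20 % lost among controls, expected completers become equal when invited-arm attrition is 1 − 80/140 = 42.9 %, which is 60 of 140. That would happen if none of the 40 invitees expected to be unreachable or to decline gave follow-up data and 20 of the 100 who enrolled were also lost. So the number of completers could mask the arms in an unfavourable case. The number randomised could not: it stays 140 v 100.

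**Receipt data.** The CACE analysis divides the invited group into receivers and non-receivers and seeks a comparable subgroup among controls. The Discussion says that full crossover from control is not possible. A receipt indicator therefore identifies the invited arm, and the model cannot be fitted without knowing which arm was offered the intervention.

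**Which stated choices depend on the arms.** The adjustment rule does: it is a comparison between arms with an unstated threshold. The primary score weights do not: they come from a logistic regression of prevalent HIV infection at study recruitment, and people who had tested positive are not eligible for this trial.

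**The case against.** The strongest reply accepts the count but disputes that it matters. A baseline imbalance looks the same whichever arm carries which label, and the decision on adjustment can be taken before any outcome is seen. This largely stands, and it is why the likely bias is modest. It does not remove the point, because with no threshold the decision is a judgement, and a judgement can be swayed by knowing which arm an imbalance disadvantages.

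A second reply is that an analysis plan not shown may name covariates, stage the data release or give CACE to another analyst. That would limit the harm. It would not make the unqualified sentence true of an analyst who runs the analyses described, since the primary set alone reveals the arms.

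A reader might infer more than the documents support:

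- That the weights of the primary score could be steered by arm. They are fitted to recruitment data on prevalent infection, where trial arm plays no part.
- That the imputation model is another exposed choice. Its detail is commonly left to the analysis plan, so its absence here shows nothing.
- That text-message logs and the mHealth questionnaires unmask the analyst. They are assigned to the nested descriptive and qualitative studies, and nothing says they reach the trial analyst.
- That every analysis file must carry a receipt flag. A modified intention-to-treat file of about 100 v 100 can be cut by whoever holds the codes and passed on without one; only CACE needs it.
- That the Limitations section withdraws the claim by saying blinding is not possible. The reason given there concerns assessors, not the analyst.

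**Conclusion.** The analyst-blinding statement does not hold as written. With the stated allocation of 140 v 100 and a primary set of all randomised participants, arm codes are decoded by a count, and CACE requires the arm to be known. This rests on the two stated arm sizes and on the analyst receiving the full randomised set. It does not depend on attrition or on the split of controls by site. The 1:1 ratio stated elsewhere conflicts with 140 v 100 and needs reconciling as a separate matter.

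The consequence is limited. The adjustment rule is the one stated analysis choice shown to be exposed, and it uses baseline data. The documents do not support saying that the primary result is biased or that covariates would be chosen by looking at adjusted outcomes. The point is worth correcting because the safeguard would be reported although it did not operate, and because it can be made real cheaply.

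**What to change.** 1. Reword the Blinding section to say that the analyst is blinded until the primary analysis code is locked.
2. Name the adjustment covariates in advance, for example the stratification factors (site and injection drug use at the last visit) and the baseline score, in place of the rule based on a between-arm baseline comparison.
3. Have the analyst write and lock the primary intention-to-treat code on data with permuted arm labels and no receipt flag. Permuted labels keep groups of 140 and 100, so the code runs, but the count no longer says who is in which arm.
4. Have the statistician who holds the allocation codes release the true labels, and run the locked code. Release the receipt flag, for the modified intention-to-treat and CACE analyses, only after the intention-to-treat result is filed.

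The cost is a change of wording and one staged data release, with no extra staff. The downside is that covariates can no longer be chosen after seeing the arms. A chance imbalance in an unlisted factor would be reported but would not alter the pre-specified analysis.
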